# Using information and communication technologies (ICTs) to solve the repressed demand for primary dental care in the Brazilian Unified Health System due to the COVID-19 pandemic: a randomized controlled study protocol nested with a before-and-after study including economic analysis

**DOI:** 10.1186/s12903-022-02101-9

**Published:** 2022-04-07

**Keywords:** Child, Teledentistry, Telemonitoring, Teleorientation, Coronavirus infections

## Abstract

**Background:**

With the COVID-19 pandemic, thousands of children had their dental care interrupted or postponed, generating a pent-up demand for primary care. To minimize the impact of this outage, information and communication technologies (ICT) could be an alternative. The aim of this study is to elucidate the impact of implementing the ICTs in primary dental care for children on resolving the pent-up demand for primary dental care to children in the national health system service (SUS) due to the COVID-19 pandemic.

**Methods:**

Different research strategies are being proposed to demonstrate such effect and extrapolating findings to a real-world context to guide further research, practice and policies: two clinical trials (one randomized controlled by the waiting list trial (RCT) and a before-and-after study), one simulation study to prospect trial results to a broader population and three economic evaluations using different effects. Children enrolled in a reference dental unit will be invited to participate in the before-and-after study for trials. The first 368 families will be randomized for the RCT to the intervention vs waiting list. All participants will receive the intervention, but the waiting list group will be assessed before the intervention is available for them. The intervention comprises standardized non-face-to-face primary dental care using the V4H platform. The problem-solving and the family's perception will be the primary outcomes set for the before-and-after study and RCT, respectively. They will be measured 2 weeks after randomization. Based on trial findings, we will develop theoretical models to estimate how the intervention could benefit the population included in the national health system.  Three economic evaluations will be carried out considering different trial effects (cost-effectiveness analyses). A societal perspective and the pandemic time horizon will be considered. Possible social impact (inequalities) will also be explored.

**Discussion:**

This ongoing trial may be an essential contribution to clarify positive and negative aspects related to the use of technologies for non-face-to-face dental care for children. Trial products may bring relevant contributions to the pandemic context and the post-pandemic period. Potential benefits may be feasible to implement and preserve in the health system even in the post-pandemic period.

*Trial registration* Clinicaltrials.gov registration NCT04798599 (registered March 2021).

**Supplementary Information:**

The online version contains supplementary material available at 10.1186/s12903-022-02101-9.

## Background

A drastic repressed demand for primary dental care has been created since the beginning of the COVID-19 pandemic [1–3]. Due to the health professionals' higher risk of contamination [4] associated with aerosol generation [5, 6] dentists have been orientated to postpone elective treatments in different locations [7]. A reduction of almost 90% in primary dental care for children was noted in the Brazilian National Health System (Unified Health System—SUS) compared to the beginning of the pandemic time [8]. This scenario, therefore, contributed to thousands of children lacking primary care, both for their non-operative and operative needs, representing essential pent-up demand for Public Health and should urgently guide policies to deal with this context.

The use of technologies could be a meaningful strategy for minimizing such impact on the health systems. Teledentistry has been demonstrated to be equivalent (or even valid) to face-to-face sessions for different purposes related to primary care, as screening, consultations, orientations and referrals [9, 10]. The use of technology in dental health care has been demonstrated to result in health equity services, reduction in waiting time, and costs with treatment [9]. Its benefit has been noted, especially in school-based programs and patients with limited access to care. The pandemic has created an unexpected and unusual difficulty to access that could be overcome by using this kind of technology.

We hypothesized that using the Teledentistry resources in primary dental care for children might aid to solve some demands that do not necessarily require a face-to-face appointment. Indeed, a teleconsultation could reduce the waiting time for seeing a professional and comfort the patients/parents, solve patients’/parents' doubts, orient about habits and conducts, and refer to other services when necessary. In addition, the pandemic could be a window of opportunity to introduce regular oral health care [11], and the potential for implementation should also be explored.

On the other hand, some barriers have also been associated with this promising alternative, such as infrastructure, patients' motivation/compliance, stakeholders' resistance, and legal and security issues [9, 12]. They are more frequent in developing countries, in which there is a lack of robust evidence about the use of this technological strategy. Indeed, very few assessment studies about ICTs have been performed in developing countries [9]. Understanding which possible adaptations to the intervention are needed to overcome these barriers is crucial to its effective implementation because the core components of the intervention must be retained for effectiveness [13].

Broad implementation of any intervention in diverse practice systems demands understanding the perspectives of different stakeholders who will affect and be affected by such intervention [14]. When planning health actions, users' judgment/satisfaction with health services are also imposing indicators to consider [15]. Besides, the allocation of resources is another relevant aspect for planning actions within health services. It is worth knowing whether the proposed strategy represents an efficient allocation of resources to substitute what has been currently done (or in such case, what is not being done). Thus, economic evaluations can be used as additional tools for making political and economic decisions [16–18].

The present trial aims to elucidate the impact of implementing the ICTs in primary dental care for children on resolving the pent-up demand for primary dental care to children in the SUS due to the COVID-19 pandemic. In this sense, different research strategies are being proposed to demonstrate such effect and extrapolating findings to a real-world context to guide further research, practice and policies. Trial products may bring relevant contributions to the pandemic context and the post-pandemic period.

The following specific objectives are defined:To identify the repressed demand for the outage of dental care and the benefits and difficulties, as well as the perception of users, in the implementation of new strategies of non-face-to-face care based on technology (teleservice), using a primary care cell unit for children and prospecting, through models, this situation for the scenario of the Unified Health System (SUS).Perform different forms of economic evaluation to measure whether the gains achieved with the implementation of teleservice (telescreening, teleorientation and telemonitoring) compensate for the additional costs possibly associated with it, or whether they are associated with a long-term resource savings, considering the implementation  dimensioned for the Brazilian public health system.Explore how the introduction of these technologies could benefit the SUS in the trans and post-pandemic period, contribute to the correction of possible inequities in the health care and other social aspects, as well as result in possible differences when different Brazilian scenarios are explored.

## Methods

This manuscript was written following the Standard Protocol Items: Recommendations for Interventional Trial (SPIRIT) [19] for clinical studies (Additional file 1) and potential items to be included in Health Economics Analysis Plans (HEAPs) for Trial-Based Economic Evaluations [20] for economic evaluation (Additional file 2). The primary trial was registered on Clinicaltrials.gov (TeleDent-COVID19—registration NCT04798599) in 2020.

### Study setting

A mobile dental unit was chosen as the reference unit to collect outcomes related to implementing technologies for primary dental care for children. This unit is in the Greater São Paulo and has been providing dental care for children since 2014 (FAPESP-2012/50716-0). Since then, approximately 10,500 operative and non-operative dental appointments have been accomplished.

Currently, 750 children are enrolled for being cared for in this unit. They have participated in some previous clinical trials whose Recruitment was done at the unit. In the pre-pandemic period, nearly 40 children were regularly seen per week. Dental care was part of research protocols developed in the unit and fulfilled patients' needs. Emergency care was also part of the routine. On average, eight emergency visits were performed per month. Toothache and prolonged tooth retention were the main reasons for them. Due to the current pandemic scenario, face-to-face care was suspended, causing our team to seek new alternatives for welcoming these patients. Then, an intervention for non-face-to-face caring using technologies was designed to overcome such situations and the Teletrailer program was launched (Fig. 1).

**Fig. 1 Fig1:**
[figure not shown]
Teletrailer program logo—program for non-face-to-face primary dental care for children, the intervention tested in TeleDent-COVID-19

### Trial design and participant timeline

A randomized controlled trial (RCT) was designed to be nested in a before-and-after study to cover different outcomes explored when implementing the ICTs in primary dental care for children (Fig. 2). A health system-simulated scenario was set using a mobile dental unit as a cell unit for primary data collection.

**Fig. 2 Fig2:**
[figure not shown]
The architecture of studies proposed to demonstrate the effect of implementing the non-face-to-face primary dental care for children using technological resources and extrapolating these findings to a real-world context to guide further research, practice and policies

The primary outcome was set in the RCT. Such a study was controlled by participants' waiting list and measures users' /parents' perceptions about the health care offered and permitted using the participants waiting for dental care as reference (Fig. 2). The before-and-after study collected data related to the natural implementation of ICT in the Teletrailer program.

The situation before the non-face-to-face intervention was considered the control to the before-and-after study. To measure it, besides the consultation, researchers will establish telephone contact with all registered patients and collect information about pain during the trans pandemic period, search for dental care in other public or private units and other possible complaints that occurred during this period. Besides, information reported during the teleconsultation will be considered as that. Thus, we will have an overview of the impact of the outage of care in the unit after social distancing. Outcomes are related to pen-up demand solving, as well as the strengths and barriers of the program implementation. They were collected in the "after" moment, two weeks after implementing the intervention. Other outcomes in this study design were collected after one year from intervention as detailed further (Figs. 2, 3).

**Fig. 3 Fig3:**
[figure not shown]
Schematic diagram representing the workflow for conciliating the studies **and** the time schedule of enrolment, interventions, assessments, and visits for participants

Included children will continue to be followed every six months, following the systematic proposal when implementing technology-mediated interventions until the return of face-to-face activities is possible and the entire structure of the dental unit is prepared for dental care. The systematic recording of new complaints and complications will be maintained both during the consultation and in spontaneous contacts of the participants.

Apart from these clinical studies, simulation models will be used to prospect the ideally found in the cell unit to a SUS-simulated scenario, predicting the actual implementation on regular health units in SUS. Economic and social impact (including inequalities exploration) will also be explored in secondary analyses exploring data collected in the mentioned primary studies (Fig. 2). The following sessions will be described considering each of the research strategies mentioned, as illustrated in Fig. 2. The individual items related to the study design were described separately for each one. For the clinical studies, some sessions were merged to a broader comprehensive.

### The before-and-after study

#### Main purpose

Measuring the natural impact on pent-up demand solving and other effects resulting from telecare implementation in primary care for children.

#### Participants: eligibility criteria

All children enrolled for dental care in the unit were eligible for this trial. Their parents/caregivers will be contacted and invited to be part of the non-face-to-face program. After several attempts, children who cannot be contacted will be excluded from the sample. Children or guardians who do not agree to participate in the research will be computed as an outcome, as described further. In this case, teleconsultation may be performed if they desire, but without other data collection for research purposes.

#### Interventions

The intervention is the non-face-to-face strategy used in the Teletrailer Program, based on teledentistry resources to minimize the interruption of primary dental care (prevention and curative) during the pandemic. The consultation was guided by a standardized protocol (Fig. 4) and performed by a team of dentists (graduate students), also responsible for previous face-to-face care at the unit. The session was divided into three parts (Fig. 4).

**Fig. 4 Fig4:**
[figure not shown]
Standard Operational Procedures (SOP) that were used to guide the non-face-to-face consultation in the Teletrailer program

i.Recognition of the child’s and family’s condition during the pandemic (updates on medical history, current oral health condition, sought dental care in other units, need for referral, change in hygiene and diet habits).ii.Situational recognition on habits related to oral health (diet, hygiene and other oral-related habits), followed by
individualized orientations about them.iii.Personalized management of patients’ and families’ needs according to their reports and complaints, looking to solve their specific demand. The management strategy will follow a pre-defined and standardized structure based on the best evidence available in the subject. Standard strategies should be used depending on which patients' report (Fig. 5).

**Fig. 5 Fig5:**
[figure not shown]
Clinical decision-making protocol to meet the patients’ and families’ reported demands related to oral care

An electronic form was created to guide consultation and permit data collection. The data collected by the form was stored under the supervision of the principal investigator ([name]), in cloud storage and on a USB stick.

The teleservice will be carried out through a digital platform (Video for Health—V4H). This platform is innovative, 100% Brazilian, created by the Research and Extension Center (Lavid) of the Informatics Center in Federal University of Paraiba (UFPB) in partnership with the Federal University of São Paulo (Unifesp) and financially supported by the National Network of Teaching and Research (RNP). The Teledentistry Center of Dental School, University of São Paulo contributed to adapting platform functionalities to the context of the SUS and the private sector in Brazil. The platform offers confidentiality in data traffic between participants, preservation for the time it is necessary to recover recorded videos, secure recording (with encryption) and registration in blockchain or trust protocol and a distributed registration technology to guarantee security in using it.

The operators were trained to use the V4H platform resources by expert researchers in teleservice and V4H development and support staff. Besides, they will receive the necessary technical support from the V4H team during the study. They are also calibrated on following Standard Operational Procedures to guide the consultation in a standardized way. Families enrolled in the Teletrailer program will receive information and support to use the platform from the Teletrailer team.

#### Outcomes

As the primary outcome for this before-and-after study, we consider problem-solving, considering the participant as the measurement unit. We will consider all the complaints pointed out by patients and their families during the baseline consultation. To measure that, a 2-weeks-later interview using the same platform (V4H) will address aspects relevant to understanding if the patients' and families' demands are solved during this time. A checklist to identify possible barriers and facilitators related to each type of complaint will be employed on these interviews. The time to resolution of the complaint will be computed as a secondary outcome.

Children will also be asked to toothbrush and floss during this assessment consultation. An external assessor will check the problem-solving related to the demand for oral hygiene orientations. The guidelines for orientation will be used as the reference standard to check if the demand was solved. If the child fulfils all oriented aspects, the demand is fully solved. If at least one assessment criterion is fulfilled, it is considered a partially solved demand. Cases of non-compliance with intervention sessions or those families that give up the consultations were also considered to understand the studied service's implementation.

Other outcomes will be assessed as secondary ones. The teleservice platform will measure consultation time. Technological and non-technological difficulties during the consultation (absences or delays, non-compliance, difficulties in using the platform, accessing the internet or even the computer or mobile phone) will be registered by an external assessor in a specific file at the end of the online session. The caregivers' and child's perceptions on the use of technologies in primary dental care will be collected by specific questionnaire [21] in the two-week-later assessment.

The users' attitudes during the consultation will be evaluated. An assessor, who participates as a spectator in the videocall, will use a specific scale, PANAS [22] The scale records necessary actions to classify this outcome. Besides, a semi-structured interview using guided questions will also be performed. It intends to identify participants' and parents' perceptions and potential barriers and facilitators for receiving the non-face-to-face dental during the pandemic. Afterwards, an external examiner will assess the video recordings using the same scale and perform qualitative analysis. This external examiner will be not included in the consultation and is unaware of previous evaluations.

For this qualitative phase, individual interviews will be recorded and transcribed. For this, individual interviews will be recorded and transcribed. The software Maxqda® will be used for categorizing the recorded speeches and, later, a content analysis (CA) will be performed [23]. For this analysis, categories are created following the common themes that emerge from the transcribed text. The analysis technique consists of three major steps: (1) pre-analysis; (2) the exploitation of the material; (3) the treatment of results and interpretation. Thus, we hope to identify qualitative differences between the groups that received technology-mediated care during the pandemic period or not, which cannot be captured through quantitative methods.

Finally, long-term outcomes will also be collected. Increment in caries experience since the interruption of dental and increment (or changes) in the needs for dental treatment will be assessed one year after the intervention. Presential clinical examination will be performed focused using dmft and DMFT and dental treatment need (including untreated caries, need for restoration repair, need of gingival or periodontal treatment, need for extractions for any reason) at this time point. An examiner unaware of baseline conditions will assess these indices and needs. These outcomes will be compared to those previously recorded in participants' records, resulting in the difference between the indices between these moments.

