**Fig. 7 Fig7:**
[figure not shown]
Cost components to be valued for the economic evaluations

Direct costs will be computed considering the time of use of the teleservice. This time will be recorded on the platform and by the service professional to double-check. For the calculation for the professional cost: the salaries of professionals will be based on the official national data will be used. With this, it will be multiplied by the time spent. Sensitivity analyses will be performed using data from different regions and/or different available services/positions.

The costs for the installation and maintenance of the teledentistry system take into account the program's implementation and its continuous operation. This type of cost will consider the time spent by the team for developing the system and the cost of maintaining and using the platform. An hourly value for using the technology will be calculated based on system capacity and usage flow data per month [30] and thus the value of the time obtained. A similar strategy will be made considering the expenses related to training and training of the team to implement the strategy [31].

To value the cost of using the technology by the patient/family, the average prices for 1Mbps of internet and Kwh of energy in Brazil, taking into account the time spent in each consultation. The value for patient's and caregiver's time and caregiver will be valued using arbitrary reference values (for example, the minimum wage and/or average salary of the population) and the time spent during care.

To value the treatments received outside the dental unit, the average value per procedure was obtained from a data repository of costs related to care provided at the same unit when performing another clinical study (NCT02473107). If a child needs to perform a restoration during the period, a value is estimated based on that repository.

In the case of unresolved complaints or patients who miss the expected follow-up until the end of the pandemic, the costs of possible complications will be valued based on the expected outcomes using models.

In the case of patients who will not receive the intervention, the costs of the intervention will not be considered since face-to-face care at the time of the pandemic is suspended (Fig. 5).

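### The one-year change in treatment needs nets new needs against treated ones, so it cannot tell a need that never arose from one treated face-to-face

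*Protocol article*

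**What the plan says.** In the Protocol article, the Outcomes section of the before-and-after study sets two long-term outcomes: the increment in caries experience and the "increment (or changes) in the needs for dental treatment will be assessed one year after the intervention". The second is described as "dental treatment need (including untreated caries, need for restoration repair, need of gingival or periodontal treatment, need for extractions for any reason". An in-person examination provides both. The calculation follows: "These outcomes will be compared to those previously recorded in participants' records", "resulting in the difference between the indices between these moments".

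Other sections expect face-to-face treatment between the record and the examination:

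- Trial design and participant timeline: the telephone contact asks about "search for dental care in other public or private units".
- Interventions: the teleconsultation covers care sought in other units and the need for referral.
- Economic and social impact assessment, (c) Costs: there is a rule "To value the treatments received outside the dental unit", with a restoration during the period as its example.
- Trial design and participant timeline: remote follow-up every six months continues "until the return of face-to-face activities is possible and the entire structure of the dental unit is prepared for dental care".

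The control in this study is each child's own earlier situation. According to the Abstract, every participant eventually receives the intervention.

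**The concern.** Untreated caries, a restoration needing repair, gingival or periodontal need and a pending extraction are all present states. Each leaves the tally once somebody treats it. A difference between an old record and a new examination therefore mixes two movements in opposite directions: needs that appeared and needs that were removed by conventional care.

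The stated purpose of the study is to measure pent-up demand solving and other effects resulting from telecare. Against that purpose, a net fall in needs invites the reading that telecare held disease back. The same fall could arise because families found a chair elsewhere, while new needs were accumulating. At one year no concurrent untreated group exists to show which explanation applies.

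**Working it through.** The article gives no figure for this outcome, so there is nothing to reproduce. The check is an identity followed by an illustration.

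**Definitions, per child**
- B = needs in the earlier record
- T = recorded needs treated face-to-face before the one-year examination
- M = needs present at one year that were not in the record

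**Identity**

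Needs at one year = B − T + M.

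Change = (B − T + M) − B = M − T.

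B cancels. One treated need moves the result by −1, exactly as one fewer new need does. A need that both arose and was treated in the interval appears in neither tally.

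**Illustration (all inputs assumed; B = 2.0; T = 2.0 × share treated)**

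| Share of recorded needs treated | T | Change if M = 0 | Change if M = 0.5 | Change if M = 1.0 |
|---|---|---|---|---|
| 0% | 0.0 | 0.0 | +0.5 | +1.0 |
| 10% | 0.2 | −0.2 | +0.3 | +0.8 |
| 25% | 0.5 | −0.5 | 0.0 | +0.5 |
| 50% | 1.0 | −1.0 | −0.5 | 0.0 |

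Three different histories give a change of exactly 0.0: nothing new and nothing treated; 0.5 new with 25% treated; 1.0 new with 50% treated. Reporting M separately would give 0, 0.5 and 1.0.

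The sign turns when T = M, that is, when the share treated equals M/B. For M = 0.5 and B = 2.0 this is 25%. For a lower burden, say B = 1.0 and M = 0.3, it is 30%: the change is +0.3 at 0% treated, 0.3 − 0.1 = +0.2 at 10%, 0.3 − 0.4 = −0.1 at 40% and 0.3 − 0.6 = −0.3 at 60%.

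**Comparison with caries experience**

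A decayed tooth that is filled moves from the decayed to the filled component, and one extracted for caries moves to the missing component. The dmft/DMFT total does not fall. That increment is therefore not affected in this way.

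**Is T separated anywhere?**

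The outside-care questions serve to describe the outage, and the outside procedures serve the costing. Neither the Outcomes section nor the Statistical methods for the before-and-after study links them to the one-year difference.

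**The case against.** Several counter-arguments have weight.

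- *The article does not say that needs are counted and subtracted.* This is correct: the word count is absent, and indices could be read as dmft/DMFT alone. But the sentence on comparison has the outcomes as its subject and directly follows one that names both the indices and the needs. A difference covering needs is the natural reading. A comparison by type of need would have the same netting within each type.
- *Net remaining need is a legitimate outcome.* This stands. A need still present is unmet demand, and referral is one of the routes by which the teleservice is meant to work. Treatment after a referral may fairly be credited to it. The net figure, however, cannot separate that from care sought independently.
- *The caries increment covers part of the gap.* This also stands for new caries. It leaves restoration repair, periodontal need and extractions for other reasons uncovered.
- *The amount of intervening treatment may be small.* Care at the unit was suspended, and the Background reports a fall of almost 90% in children's primary dental care in the SUS. The article gives no rate for these children, so a low T is plausible but not established.
- *The article condenses a fuller document.* Scoring detail may be there. The point rests only on the comparison that the article itself fixes.

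A reader might infer more than this: that the long-term result is bound to favour telecare, that a large share of recorded needs will have been treated, or that the unit will have treated children before the one-year examination. The documents support none of these. They give no treatment rate and no reopening date, and they do not say that the unit treats children before that examination.

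**Conclusion.** The point holds for the treatment-need outcome. As naturally read, its one-year change equals M − T and cannot distinguish needs that did not arise from needs treated face-to-face, whether elsewhere, after referral, or at the unit if it has reopened. The identity needs no assumed values; it needs only that the planned difference covers needs and that a treated need leaves the tally.

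The size is unknown. The tables show the mechanism and are not estimates. With a small T the distortion is small; the sign changes only once the share treated exceeds M/B.

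This is a long-term secondary outcome of the uncontrolled component. Both primary outcomes, the RCT sample size (306, raised to 368) and the dmft/DMFT increment stand apart from it. What is at risk is the interpretation: a net fall should not be reported as a telecare effect on the strength of this difference alone.

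**What to change.** Keep the net change and label it as the change in remaining unmet need. Report beside it, by tooth or by type of need:

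1. new needs that were not in the earlier record;
2. recorded needs still present at one year;
3. recorded needs treated since the record, noting where possible whether treatment followed a teleservice referral.

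The sources are largely in place: the decayed, missing and filled components of the planned examination, the earlier records, and the outside-care information already requested. A filling now present in a tooth recorded as sound also reveals a new need that was treated in between. State that a net fall will not be interpreted as a telecare effect without this split.

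Do not add a separate analysis of children with and without face-to-face treatment as a way of isolating the effect. Receiving treatment is a post-intervention event driven by symptoms, severity and referral, so the comparison would introduce selection. If shown, it should be labelled descriptive only.

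The cost is mainly definition and analysis wording. The downside is dependence on the detail of old records and, for needs not visible in dmft/DMFT, on caregiver report. The planned follow-up records new complaints and complications and is not described as recording treatment tooth by tooth, so some treated needs may be classifiable only by type.
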